### Framework of Activities

#### Assessment of Patients’ Perceived Needs for Self-Management Support

A 10-item questionnaire, the Self-management Assessment Scale (SMASc), assessing patients’ needs for SMS, has been developed within the project, and its validity and reliability have been tested and found acceptable (manuscript, [name] et al, 2018, unpublished data). The questionnaire is a person-centered measure of the type of iSMS that is needed for each person. The questionnaire includes subscales knowledge, routines, goals, emotional support, and social support and is generated from the literature on patient perspectives on chronic illness or T2D and self-management challenges.

#### Co-Designed Workshop

Several activities to prepare for the co-design and participatory workshop have been completed. Individual interviews among persons with T2D treated in Swedish primary health care centers (HCCs) were conducted to gain an understanding of their perceptions about and experiences of using eHealth services for self-management [19]. Furthermore, focus group interviews have been conducted with primary health care nurses about their perceptions of working with digital resources and iSMS in the care of people with chronic conditions, including T2D [20]. These earlier studies have been the basis for the development of the intervention.

A multistakeholder workshop was held on 16 September, 2016, which 27 invited participants attended, (5 were academic representatives, 6 were living with T2D, 2 were relatives of persons living with T2D, and 1 was a medical doctor and also the head of primary health care in the County Council). Furthermore, 10 were DSNs, 1 worked with information technology development in the County Council health care service and lastly, 2 were representatives of a Swedish company that develops apps for people living with diabetes.

The purpose of the workshop was to involve various participants in ideas about the design of the app, thereby influencing and developing the intervention and choice of app. During the workshop, the potentials and limitations of SMS with digital technology were explored and how SMS could be designed to motivate self-management in everyday life, at work and in the patients’ daily life with diabetes, was considered. The workshop used both focus group discussions with mixed groups of representatives and mentometers to answer questions. During the workshop, it was revealed that the most important needs were related to person-centeredness, accessibility, and effectiveness. The summary of the results from the workshop suggested guidelines for setting up the intervention (manuscript, [name] et al, 2018, unpublished data) and provided guidance in planning the 1-year intervention, expected to start in autumn, 2018.

### Intervention

DSNs will be trained in using the SMASc questionnaire to score the SMS needs. They will also be trained in using and instructing participants how to use the app. Furthermore, they will be taught how to use the Web page, with diabetes facts and illness integration support, included in the project. All recommendations to patients will be based on patients’ stories and expressed needs as well as patients’ scores on the SMASc questionnaire to make the individual plans person-centered.

Both the intervention and control groups will continue with their usual diabetes care, including all medical visits, tests, and diabetes support programs. The starting point for the 4-months’ intervention is the baseline scoring on the SMASc questionnaire, resulting in a tailored person-centered plan for self-management through monitoring and interaction with DSN. The intervention group will receive the app, including instructions on how to use it, and the Web page with diabetes facts, as described above. DSNs will also assist in installing the app on the participants’ smartphone or tablet. The software can be personally tailored according to the participant’s needs to provide a personal overview of how food, exercise, medicine, blood sugar, and BP interact. The participants can evaluate food intake, blood glucose levels, insulin, medicine intake, exercise (physical activity), and weight over time and receive reminders if they would like them. Participants may, if they wish, choose whether their DSN should have access to their data or not. The system will maintain logs of all outgoing and incoming messages, and incoming blood glucose values will be graphed by the system, which individuals can view.

#### Diabetes Management App

The diabetes management app, mySugr, offers data tracking and coaching services for people living with type 1 or type 2 diabetes. The mySugr App is a registered certified medical device, and carries the CE marking (Medical Devices Directive 93/42/EEC). Furthermore, the app is registered with the Food and Drug Administration, and per se, it is required to meet the highest of data security and reliability standards. The app is available for iOS and Android operating systems for mobile access. There is easy manual input of data, which may be synchronized with selected glucose meters via Bluetooth, and one can easily log in and maintain a record of diabetes clinical data. The app uses these data to provide analysis and trending results. Currently, the app offers features for self-monitoring of diet, exercise, blood sugar, smoking, weight, and medication as well as gamification to support improved self-management. Reminders and self-reflection are linked to these areas, as are statistics and visualization [31-33].

#### Website

The website (www.t2d.se-in Swedish) is a complement to the app with opportunities for social support, factual information, and links for interaction with other patients through discussion forums as well as opportunities for interaction and support from the diabetes nurse via a messaging feature.

### Power Calculation and Sample Size

A power calculation showed that with a sample of 46 participants per group, a power of 80% with an alpha<.05 will demonstrate significant HbA_1c_ difference of 6 mmol/mol between the groups and a within-group SD assumed to be 9 [10]. This means that there is an 80% likelihood that the study will yield a statistically significant effect and allow us to conclude that the mean HbA_1c_ differs between the intervention group versus the control group. To compensate for dropouts, the study needs to enroll 46 participants per group for a total of at least 120 participants.

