**Methods:**

This study is a 12-month, 3-armed, nonblinded randomized controlled trial (RCT), which will be conducted in 6 primary health care centers (HCCs) in northern Sweden. Eligible participants will be randomized to either an intervention group (n=46), a control group (n=46), or an external group (n=46) for comparison. The intervention group will receive the mobile app, and the control group will receive a minimal intervention (diabetes brochure) and the usual standard of care. Changes in glycated hemoglobin (HbA_1c_) will be the primary outcome measure.

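### The sample-size figures contradict each other: 46 evaluable per group gives about 89% power rather than 80%, 46 is also the dropout-compensated enrolment, and the total of 120 matches neither 92 nor 138

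*Protocol article*

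**What the plan says.** Under Power Calculation and Sample Size, the protocol article opens with "A power calculation showed that with a sample of 46 participants per group, a power of 80% with an alpha<.05". The inputs are a "difference of 6 mmol/mol between the groups" and a "within-group SD assumed to be 9", and the comparison is intervention against control. Whether the test is one- or two-sided is not stated. The paragraph ends: "To compensate for dropouts, the study needs to enroll 46 participants per group for a total of at least 120 participants". No dropout rate is given.

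The Methods part of the abstract sets the group sizes: "Eligible participants will be randomized to either an intervention group (n=46), a control group (n=46), or an external group (n=46) for comparison". The Inclusion Criteria repeat 46 for each group and say that the external group comes from two other centres. Randomization and Blinding describes 1:1 allocation of participants to intervention or control. Study Population and Sampling, however, speaks of a clustered design for patient recruitment.

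**The concern.** The paragraph gives 46 two roles. In the first sentence it is the number that yields 80% power, and so the number needed for analysis. In the last sentence it is the number to enrol after allowing for dropouts. Both hold only if nobody drops out, in which case there is nothing to compensate for.

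The stated inputs do not lead to 46 at 80% power, and 46 per group does not lead to 120 in total.

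At stake is the justification for the primary comparison. A reader cannot tell whether 46 is the evaluable or the enrolled number, how much attrition was allowed for, or how many participants the trial intends to recruit.

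**Working it through.** **Inputs.** From Power Calculation and Sample Size: difference 6 mmol/mol, SD 9, alpha .05, power 80%, two groups. From Randomization and Blinding: 1:1 allocation. My assumptions: two-sided test, individual randomisation.

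**1. Attempt to reproduce 46 at 80% power.** By the normal approximation,

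n per group = 2 × (z₀.₉₇₅ + z₀.₈₀)² × (SD/difference)² = 2 × (1.960 + 0.842)² × (9/6)² = 2 × 7.85 × 2.25 = 35.3, so 36.

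The two-sample t-test gives 36.3, so 37. The stated 46 is not reproduced. A one-sided test needs only 28 to 29 per group, which is further away.

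**2. Power at 46 evaluable per group.** The standardised difference is 6 / (9 × √(2/46)) = 3.197. Power by the normal approximation is Φ(3.197 − 1.960) = Φ(1.237) = 89.2%. Results by the t-test:

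| Evaluable per group | Power |
|---|---|
| 37 | 80.8% |
| 40 | 83.8% |
| 46 | 88.6% |

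For 46 to give exactly 80%, the SD would have to be about 10.2 or the difference about 5.3 mmol/mol. The article states neither.

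**3. 46 as an enrolment figure.** If 37 are needed for analysis, 46 enrolled allows a loss of 1 − 37/46 = 19.6%. Working forwards with 20% loss, 36/0.80 = 45 and 37/0.80 = 46.25, so 47. Thus 46 is plausible as an enrolment figure at roughly 20% dropout. That rate is back-calculated here; the article does not state it. If 46 were instead the evaluable number, any allowance for dropout would take enrolment above 46.

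**4. The total.** Two randomised groups: 2 × 46 = 92. With the external group: 3 × 46 = 138. The figure 120 would be 3 × 40 or 2 × 60, and neither 40 nor 60 per group appears in the article. Reading 120 as evaluable participants (3 × 40, a 13% loss from 46) does not restore 80% either, because 40 per group gives 83.8%. The gap to three full groups is 138 − 120 = 18.

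**5. Dependence on the unit of randomisation.** The 89% holds only if individuals are randomised. For illustration, assume allocation by centre, 23 participants per centre and an intraclass correlation of 0.01 to 0.05; none of these values is in the article. The design effect 1 + 22 × ICC is then 1.22 to 2.10, and 46 per group is worth 46/1.22 = 37.7 down to 46/2.10 = 21.9 independent participants. Power falls to about 82% and 58% respectively, before any penalty for the small number of centres.

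**The case against.** - **An unstated method may lie behind 46.** A t-test at alpha .025 (two comparisons) needs 45 per group and gives 81.9% at 46. A three-group analysis of variance with means 6, 3 and 0 also needs 45 and gives 81.5%. Either could be the source. However, the paragraph states alpha .05 and a two-group comparison, so if one of these was used, the stated alpha or test is wrong and the text still needs correcting. What stands is that only the sponsor can say where 46 came from.
- **The error is on the safe side, and 138 does satisfy a floor of 120.** Both are true under individual randomisation. A reader might infer that the trial is underpowered, or that the team could stop 18 participants short. The documents do not support either reading. On the stated inputs 46 is more than enough, the same sentence fixes 46 per group, and the abstract and Inclusion Criteria repeat it. Even 40 evaluable per group would give 83.8%.
- **The target difference is clear.** A reader might infer that one cannot tell what difference the trial is powered for. The paragraph says 6 mmol/mol.
- **The 80% sentence looks unconditional.** It says "there is an 80% likelihood that the study will yield a statistically significant effect". It directly follows, and explains, the sentence that gives the 6 mmol/mol difference, so the condition is supplied by context.
- **This is a condensed article.** The point is not that something is left out, but that the figures it does print cannot be reconciled.

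**Conclusion.** The inconsistency is real and lies within one paragraph. On the stated inputs, with a two-sided test and individual randomisation, 80% power needs 37 evaluable per group; 46 evaluable gives 88.6% (89.2% by the normal approximation), almost 9 points above the stated 80%. That 46 serves as both the 80%-power number and the dropout-compensated number is a contradiction that needs no calculation. The total of 120 agrees with neither 92 nor 138.

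This is an error in the stated justification. It does not show that the trial is too small: under individual randomisation the planned enrolment keeps 80% power with up to about 20% loss. That reassurance does not carry over to allocation by centre, and the article's description of the unit of randomisation is not consistent.

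**What to change.** Rewrite the paragraph so that five figures agree: evaluable number per group, its power, dropout allowance, enrolment per group, and total. Replace the total of at least 120 with 92 randomised plus 46 external, 138 in all.

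One wording that fits the stated inputs: with a two-sided alpha of .05 and individual randomisation, 37 evaluable participants per group give 80% power for a difference of 6 mmol/mol with SD 9; enrolling 46 per group tolerates up to about 20% loss. This is an example only. The sponsor must confirm the dropout rate, alpha and test actually used, and if 46 came from another calculation, state that one instead.

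State that the figure assumes individual randomisation, and reconcile this with the clustered design mentioned under Study Population and Sampling. If centres are the unit of allocation, the power must be recalculated.

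Under individual randomisation the cost is wording only; the planned group sizes and recruitment do not change.

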### Randomization and Blinding

Eligible participants will be randomized to either the intervention or the control groups in a 1:1 ratio. Owing to the nature of the intervention, participants will be aware of their treatment allocation. Therefore, the blinding of participants will not be possible. However, DSNs in charge at HCCs will not be involved in the randomization, preparation of the envelopes with study information, or statistical analyses.

### Study Population and Sampling

Sampling will be conducted both at the organizational HCC level and at the patient level. First, primary health care managers at HCCs in a county in northern Sweden have previously received verbal and written information on the purpose of the study and the implementation process as well as inclusion criteria, and all have accepted participation. After receiving consent from primary health care managers, DSNs at 6 HCCs accepted participation, got verbal and written information about the study, and were invited to participate in the co-design and participatory workshop and the RCT study and were further asked to collaborate in patient recruitment using a clustered RCT design.

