#### Control Groups

The control groups will be included in the data collection of laboratory values as well as questionnaires, similar to the intervention group. In addition to this, they will receive the usual care and take part in a minimal intervention in the form of a brochure about self-management of diabetes.

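### The article contradicts itself on the unit of randomisation (participants or health care centres), and its sample size fits only the participant reading

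*Protocol article*

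**What the plan says.** Three places make the participant the unit of allocation. Randomization and Blinding states: "Eligible participants will be randomized to either the intervention or the control groups in a 1:1 ratio". The Abstract and Inclusion Criteria also speak of randomising eligible participants into groups of 46.

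Study Population and Sampling describes sampling at both the HCC and the patient level. It then says that the nurses at 6 HCCs "were further asked to collaborate in patient recruitment using a clustered RCT design". No section says that HCCs are, or are not, the allocated unit.

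Power Calculation and Sample Size opens "A power calculation showed that with a sample of 46 participants per group" and assumes a "difference of 6 mmol/mol between the groups", with "a within-group SD assumed to be 9". It gives no ICC, cluster size or design effect. Data Analyses commits to intention to treat by randomised group and names no model.

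Inclusion Criteria adds an external comparison group recruited from 2 different HCCs. Whether these 2 are among the 6 is not clear, so the two randomised arms could draw on 6 HCCs or on 4.

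**The concern.** The unit of randomisation settles how allocation lists are made, which analysis is valid and what the power statement means. If patients are randomised within HCCs, each HCC contributes to both arms and the two-mean calculation is the right kind. If whole HCCs are randomised, patients in the same HCC are correlated and the treatment contrast is estimated from only 4 to 6 independent units. The calculation as written then no longer describes the trial. Once HCCs have been allocated, too few clusters cannot be repaired at the analysis stage.

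This is not detail left to a fuller document: the article makes two statements about design that cannot both hold.

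**Working it through.** **Inputs from the article:** difference 6 mmol/mol, SD 9, alpha 0.05 (taken as two-sided), power 80%, 46 per group, 6 HCCs, of which 2 may serve only the external group.

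**Assumed:** ICC 0.01 to 0.05, because the article gives none; equal cluster sizes; all 46 per arm analysed unless stated.

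**Step 1: the article's own figure, without clustering.** n per group = 2 × (1.960 + 0.842)² × 9² / 6² = 35.3, so 36 (37 by t-test). With 46 per group, SE = 9 × √(2/46) = 1.877 and 6/1.877 = 3.197. Power = Φ(3.197 − 1.960) = 89%. So 46 for 80% does not reproduce as an unadjusted figure. It is close to 36 or 37 inflated for about 20% dropout (36/0.8 = 45; 37/0.8 = 46.25, so 47), but no dropout rate is given. Under individual randomisation there is therefore slack, not a shortfall.

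**Step 2: HCC as the unit.** With k HCCs per arm, m = 46/k, which is 15.3 for k = 3 and 23 for k = 2.

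- Design effect: DE = 1 + (m − 1) × ICC
- Standardised effect: λ = 3.197/√DE
- Power, design effect only: Φ(λ − 1.960)
- Power, cluster-level test: noncentral t with noncentrality λ on 2k − 2 df
- Type I error of an analysis that ignores clustering: 2 × (1 − Φ(1.960/√DE))

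| HCCs per arm (df) | ICC | DE | λ | Power, design effect only | Power, cluster-level t | Type I error if clustering ignored |
|---|---|---|---|---|---|---|
| 3 (4 df) | 0 | 1.00 | 3.20 | 89% | 67% | 5% |
| 3 (4 df) | 0.01 | 1.14 | 2.99 | 85% | 62% | 6.7% |
| 3 (4 df) | 0.02 | 1.29 | 2.82 | 80.5% | 57% | 8.4% |
| 3 (4 df) | 0.05 | 1.72 | 2.44 | 68% | 46% | 13.5% |
| 2 (2 df) | 0 | 1.00 | 3.20 | 89% | 42% | 5% |
| 2 (2 df) | 0.01 | 1.22 | 2.89 | 82.5% | 37% | 7.6% |
| 2 (2 df) | 0.02 | 1.44 | 2.66 | 76% | 33% | 10.2% |
| 2 (2 df) | 0.05 | 2.10 | 2.21 | 60% | 25% | 17.6% |

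**Step 3: the ICC at which 80% is lost by design effect alone.** 46 per arm tolerates DE = 46/35.32 = 1.302.

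- 3 HCCs per arm: 0.302/14.33 = 0.021
- 2 HCCs per arm: 0.302/22 = 0.014

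If only 40 per arm are analysed (the article's minimum total of 120 divided by 3 groups), DE may reach 40/35.32 = 1.1325. The thresholds are then 0.1325/12.33 = 0.011 and 0.1325/19 = 0.007.

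**Step 4: can more patients repair it?** With 3 HCCs per arm and 4 df, 80% needs about 64 per arm at ICC 0, 80 at 0.01 and 109 at 0.02. At ICC 0.05 it is not reached with up to 5000 per arm. More HCCs would be needed, not more patients.

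**The case against.** The text is not evenly split. Three places randomise participants. Patients are phoned individually for consent to the randomisation process. Nurses from all 6 HCCs are to be trained to introduce the app, which fits poorly with whole HCCs being controls. The cluster wording appears once, attached to recruitment in a paragraph on sampling, and may loosely mean recruiting by centre. This stands: the individual reading is the better supported one, and on it clustering costs no power.

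It is also fair that the shortfall under the cluster reading is conditional. A reader might infer that 80% fails in every case if HCCs are randomised. By design effect alone it does not: with all 46 analysed, 3 HCCs per arm still give 85% at ICC 0.01. The general failure comes from the degrees of freedom, which depend on an analysis the article does not specify.

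A reader might further infer that the planned analysis has an inflated type I error. Data Analyses names only inferential statistics and does not commit to treating patients as independent. The inflation therefore describes what would happen if clustering were ignored, not what is planned.

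Finally, a reader might infer contamination under individual randomisation. The article says "The starting point for the 4-months’ intervention is the baseline scoring on the SMASc questionnaire", and of the controls, "The control groups will be included in the data collection of laboratory values as well as questionnaires, similar to the intervention group". It does not say that nurses see or act on controls' SMASc scores, and it ties the tailored plan to the intervention. It gives no basis for sizing any leakage. That inference is not supported and forms no part of this point.

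None of this removes the contradiction itself, which remains in the prose.

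**Conclusion.** The article contradicts itself on the unit of allocation, and its sample size is consistent only with randomising participants. That much needs no assumption.

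The numerical consequence depends on which statement is true:

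- **Participants randomised (better supported):** no shortfall from clustering. This does not confirm the stated 80%: at the stated inputs, 46 per arm gives about 89%.
- **HCCs randomised:** an analysis with degrees of freedom matched to 4 to 6 clusters falls short of 80% at every ICC, including 0. Judged by design effect alone, the outcome turns on whether the ICC exceeds the thresholds in step 3. An analysis that ignored clustering would have a type I error of about 7% to 18% over the assumed ICC range, instead of 5%.

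The figures for ICC above 0 rest on an assumed range, and all of the cluster figures assume equal cluster sizes. The article alone does not support calling the trial underpowered as planned.

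**What to change.** State one unit of randomisation before allocation starts, and make Randomization and Blinding, Study Population and Sampling, and Power Calculation and Sample Size agree with it.

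- **If participants:** delete the reference to a clustered design, stratify the 1:1 allocation by HCC and include HCC in the primary model. Cost: a wording change, stratified allocation lists and one model term.
- **If HCCs:** replace the 80% with the cluster-adjusted power, giving the ICC and the number of HCCs per arm. Also say whether the external group's 2 HCCs are among the 6. Analyse at cluster level, or with a mixed model that has a small-sample correction. Cost: a less favourable stated power, which adding patients within the same HCCs may not restore.
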